### Clinical and laboratory parameters

In addition to the immunological profiling and outcome measures, a number of donor and recipient characteristics will be extracted from registries, databases and local hospital healthcare records where appropriate and available. Data to be extracted include donor factors of age, sex, body mass index, donor relationship to recipient, comorbid conditions and race; recipient factors of age, sex, body mass index, race, socio-economic status (SES; derived from post-code in Australia or alternative SES parameters in other countries), prior episodes of non-adherence to immunosuppressive agents or missed appointments (as recorded in healthcare records), comorbid conditions (including complex syndrome, urological, liver or cardiac diseases) and dialysis duration; and transplant-related factors of transplant era, ischaemic time, sensitization status of percentage class I and II panel reactive antibody (%PRA), types and intra-patient variability of the calcineurin-inhibitor levels; all of which are known to be associated with the clinical outcomes of interest. Information relating to measures of potential sensitization to maternal antigens, including complications in maternal pregnancy including infections, breast-feeding and prior pregnancies will be sought from respective donors (where available).

Specific outcome measures include acute rejection (and Banff classification) at any time point post-transplant (types, severity and response to treatment), allograft function (creatinine and eGFR at 3 and 6 months, then annually post-transplant), allograft failure (including causes of allograft failure) and death (including causes of death) will be extracted from ANZDATA registry or relevant sources in other countries; and kidney biopsy reports, rejection-related treatment and response to treatment, intensity of immunosuppression (therapeutic drug levels for calcineurin inhibitor [CNI] at 3, 6, 12, 24, 36, 48, and 60 months post-transplant), proteinuria (urine protein/creatinine ratios at 3, 6, 12, 24, 36, 48, and 60 months post-transplant if available) and number/duration of all-cause and cause-specific hospitalisations will be extracted from local hospital and laboratory data. The data will be entered into a password-protected database (unique to each site) at least up to 5-years post-transplant (or until allograft loss up to 10-years post-transplantation using linkage data to ANZDATA and other country-specific registries).

### Sample size calculation

The sample size calculation is based on the primary composite outcome of de novo DSA, any episodes of acute rejection and allograft loss. In our ANZDATA registry study comparing the allograft outcomes of maternal and paternal donor kidney transplants, a greater proportion of kidney transplant recipients who had received maternal donor kidneys experienced any rejection episode compared with recipients of kidneys from paternal donors (37 and 27%, respectively; *p* < 0.001) [4]. Data relating to the development of de novo DSA are not available from ANZDATA registry. Assuming that up to 40% of recipients may develop de novo DSA, acute rejection or lose their allografts within 60 months post-transplant, a sample size of 479 donor/recipient pairs (1:1 allocation to maternal and paternal door kidneys) will be required to achieve a power of 80% with a two-sided significance of 5% for detecting a difference of 0.10 between marginal proportions after applying continuity correction (and correlations score of 0.5 of at least 4 observations [for the composite outcome measures], and accounting for potential missingness of data of up to 10%) (Fig. 2). The expected recruitment of 520 parental donor/recipient pairs in the retrospective study should have adequate sample size and sufficient power to address the study question. Sample size calculation was determined using the expected time-averaged difference (TAD) between two means from continuous, correlated data using the GEE method in PASS Sample Size Software.

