**Fig. 2 Fig2:**
[figure not shown]
Projected sample size calculation using a generalized estimating equation approach with at least four repeated measures of the primary outcome, according to varying base correlation of 0.2 to 0.7 (between repeated measures) and degree of missingness of 0.0 to 0.15. A sample size of 479 donor/recipient pairs (1:1 allocation to maternal and paternal door kidneys, represented by discontinuous blue line) will be required to achieve a power of 80% with a two-sided significance of 5% for detecting a difference of 0.10 between marginal proportions after applying continuity correction (and correlations score of 0.5 of at least 4 observations [for the composite outcome measures], and accounting for potential missingness of data of up to 10%)

Between 2015 and 2018, there were 182 pediatric and adolescent patients aged ≤18 years with kidney failure in Australia who received a kidney transplants, with parental donor kidney transplants contributing 40% of total transplants. This compared with 30 patients in New Zealand (67% parental donor kidney transplants) and 30 patients in the Netherlands (30-40% parental donor kidney transplants) in the same time-period. In the United Kingdom, there were 760 pediatric and adolescent patients who received kidney transplants between 2010 and 2015, with approximately 340 (45%) parental donor kidney transplants. These recent figures suggest that the target sample size (to recruit 520 donor/recipient pairs between 1990 and 2020) is achievable.

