### Statistical analysis

Data will be presented as mean ± standard deviation (SD) or number (proportion) for continuous and categorical variables, respectively, with means and proportion compared using *t-test* and the chi-squared test where appropriate. We will develop models with different numbers of archetypes and choose which to use as the final model according to the residual sum of squares using the “elbow” method [47]. The archetypal models will assign scores based on a combination of pre-transplant immunological and clinical (donor, recipient and transplant) parameters to each recipient using the time from transplant to the composite primary outcomes of de novo DSA, any episodes of acute rejection and allograft loss; with the scores totalling 1. Each parameter will be assigned to a single archetype cluster on the basis of the highest archetype score (corresponding to “high immunogenic risk” profile, comprising of immunological risk factors). Additional models accounting for pre- and post-transplant factors (such as donor age, non-adherence) will also be constructed. A principal component analysis will be constructed to visualize the data matrix used as the input for the archetypal analysis. The principal component analyses will produce two main results: (i) a correlation circle, and (ii) a projection of the individuals. The correlation circle allows for a graphical examination of the relationships among the pre-transplant immunological and clinical parameters and the graphical parameter contribution of the axes (positive or negative contribution: vector direction; strength of the contribution: vector length when projected on the axis). We will identify distinct groups (i.e. archetypes), each comprising of a well-defined set of immunological and clinical parameters that may improve the risk stratification for “adverse immunological outcomes” for those accepting a parental donor kidney for transplantation, and separately for those who have received maternal or paternal donor kidneys. The Australian and New Zealand cohorts will be the derivation cohort for these archetypes, which will be validated in the cohorts from the United Kingdom and the Netherlands. We will next seek to build a predictive model (combined cohorts) to examine the associations between the archetype clusters and other pre-specified covariates and the primary outcome using univariate Cox proportional hazards regression models. A multivariable Cox model will be constructed by selecting covariates by Group Lasso and Doubly Robust Estimation (GLiDeR), a method of variable selection to identify confounders using an adaptive group lasso approach that simultaneously performs coefficient selection, regularisation, and estimation across the treatment and outcome models. Bootstrap resampling with replacement or subsampling without replacement will be used to investigate and quantify model stability. Separate models will be constructed for each of the secondary outcomes. The results of the model and covariates will be reviewed to ensure clinical relevance. Deviance and score residuals will be plotted to evaluate for poorly predicted individuals or individuals that may have had large influences on model parameters. The performance of the integrated prognostic model will be assessed by computing a non–time-specific area under the curve (AUC) using the measure of concordance from Somer’s Dxy statistic. For assessment of model calibration, patients will be risk-stratified on the basis of their predictive index, which is the linear combination of the product of the multivariate model β coefficients and their individual covariate values. Kaplan-Meier survival curves will then be plotted for patients who are stratified into quintiles of their predictive indices. The validation cohort’s AUC will be determined and predicted and observed mortalities will be compared. The association between archetypes and adverse outcomes will be examined in the prospective cohort, and to examine how the addition of other newly developed novel immunological assays will improve the test performance of the models.

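### The 80% power claimed for 479 pairs relies on four repeated measures of a composite that each recipient contributes only once; for a 10-point difference, 520 pairs give about 58–68%

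*Protocol article*

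**What the plan says.** All references are to the protocol article.

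- **Sample size calculation** gives the event rate: "Assuming that up to 40% of recipients may develop de novo DSA, acute rejection or lose their allografts within 60 months post-transplant". From this it derives a total of 479 pairs, split equally between maternal and paternal kidneys. The stated aim of that number is to "achieve a power of 80% with a two-sided significance of 5% for detecting a difference of 0.10 between marginal proportions". The 0.10 matches the gap in registry rejection rates ("37 and 27%, respectively" for maternal and paternal kidneys). The section adds a continuity correction, a correlation of 0.5 over at least four observations and up to 10% missingness. It names the method as the "expected time-averaged difference (TAD) between two means from continuous, correlated data using the GEE method in PASS Sample Size Software" and concludes that the 520 pairs expected give sufficient power.
- **Fig. 2 legend** confirms what is repeated: "at least four repeated measures of the primary outcome".
- **Outcome measures** defines the primary outcome as the occurrence of de novo DSA, biopsy-proven acute rejection or allograft loss up to 60 months.
- **Statistical analysis** works with the time from transplant to that composite. It uses univariate Cox models and then: "A multivariable Cox model will be constructed by selecting covariates by Group Lasso". GEE appears only in the sample size section and its figure, never as an analysis.

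**The concern.** Averaging four correlated measurements of one quantity reduces its variance, and a GEE calculation turns that into a smaller sample. The gain is real only if the analysis uses four measurements per recipient. A first event by 60 months happens once or not at all, and death or return to dialysis cannot be measured again. If the calculation takes a credit that the analysis cannot deliver, 80% is not the power of the study.

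Separately, the named procedure does not fit the stated target. A difference between marginal proportions with continuity correction is a binary-outcome calculation; a time-averaged difference between two means of continuous data is not. A reader cannot tell which was run.

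The Discussion says the findings will support or refute a maternal–paternal difference and inform families. The stated power determines how much weight a null result can carry.

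**Working it through.** **Inputs from Sample size calculation:** two-sided 5% (z = 1.960), 80% power (z = 0.842), difference d = 0.10, 1:1 allocation, m = 4 observations, correlation 0.5, continuity correction, 10% missingness, 479 pairs in total (read as a total because it is set against 520). **Assumed, because not stated:** the two arm rates. I use 40/30, 45/35 (a 40% average) and 50/40%. The correlation structure is also not stated.

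**1. Can 479 be reproduced?** The repeated-measures factor on N is:

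- exchangeable: (1 + 3×0.5)/4 = 0.625
- AR(1): [4 + 2(3×0.5 + 2×0.25 + 0.125)]/16 = 8.25/16 = 0.516

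The unpooled two-proportion total is 2×(1.960+0.842)²×[p1(1−p1)+p2(1−p2)]/d². The continuity correction takes n per arm to (n/4)×[1+√(1+4/(n·d))]².

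- 40/30, exchangeable: 706.4×0.625 = 441.5, or 481 with continuity correction. This is close to 479 but has no allowance for missingness. With every stated input it becomes 500–538.
- 50/40, AR(1): 769.2×0.516 = 396.6; 435.7 with continuity correction; /0.9 = 484. This is close and uses every stated input.
- Two means with variance 0.24, exchangeable: 4×7.849×0.24/0.01 = 753; ×0.625 = 471. This has no continuity correction or missingness.

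No single-measurement version comes near 479. The lowest found, with the registry's 37/27%, is 682.

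**2. Power with one outcome per recipient.** With n per arm and mean rate p̄:

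- Two proportions: Φ{[d − 1.960√(2p̄(1−p̄)/n)] / √([p1(1−p1)+p2(1−p2)]/n)}. For 40/30 at 479 pairs (n = 239.5): (0.10 − 0.0854)/0.0433 = 0.336, so 63.2%.
- Log-rank (Schoenfeld): HR = ln(1−p1)/ln(1−p2), events E = N·p̄, power Φ{(√E/2)·ln HR − 1.960}. For 45/35 at 520: E = 208, HR = 1.39, (7.211×0.328) − 1.960 = 0.403, so 65.7%.

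Power in %, two-proportion / log-rank. With 10% missing, 479 leaves 431 and 520 leaves 468.

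| Assumed rates | HR | 479 | 520 | 431 | 468 | Events at 520 (468) |
|---|---|---|---|---|---|---|
| 40/30 | 1.43 | 63.2 / 64.3 | 66.7 / 67.8 | 58.6 / 59.7 | 62.2 / 63.3 | 182 (164) |
| 45/35 | 1.39 | 60.8 / 62.1 | 64.4 / 65.7 | 56.3 / 57.6 | 59.8 / 61.1 | 208 (187) |
| 50/40 | 1.36 | 59.5 / 61.0 | 63.1 / 64.6 | 55.1 / 56.6 | 58.5 / 60.1 | 234 (211) |

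The registry's rejection-only rates (37/27%) give 65–66% at 479 and 69–70% at 520, before missingness.

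**3. Size needed for 80%.** By two proportions, about 712 (40/30), 751 (45/35) and 775 (50/40). With continuity correction these become about 752, 792 and 816, and dividing by 0.9 for missingness gives about 836, 880 and 907. The log-rank totals are about 697, 733 and 751 before missingness.

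**4. Difference detectable with 80% power.** I solved the same formulas for d with the mean rate held at 35, 40 or 45%. At 520 pairs d is 0.115–0.122 (HR 1.44–1.52). At 468 it is 0.122–0.129 (HR 1.47–1.56). Check at 520 with a mean of 40%: d = 0.120 gives (0.120 − 0.0842)/0.0426 ≈ 0.84, the 80% point.

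**The case against.** **The repeats could be serial DSA tests, or the components of the composite.** DSA testing follows each site's policy, with routine testing only at some centres, and it covers one component. Components are not repeats of the composite, and the Fig. 2 legend says the repeats are of the primary outcome itself. Neither reading rescues the calculation.

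**A maternal–paternal Cox test is inferred.** This stands. The Cox models are written for archetype clusters and covariates, and the third aim concerns modification by parental status. Log-rank power is therefore not shown to be the power of a specified primary test. But the sample size section itself targets the maternal–paternal difference, and a comparison of 60-month proportions shows the same shortfall. Power for effect modification is not assessed here.

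**The arm rates are not the plan's.** This also stands, so results are given across three assumed pairs; none comes near 80%.

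Three stronger readings are tempting but unsupported:

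- A reader might infer that 40% is too low because maternal rejection alone was 37%. That figure is below 40%, the 1:1 average of 37 and 27% is 32%, components can overlap within a recipient, and the documents give no DSA rate.
- A reader might take a near match to 479 as proof that the factor was exactly 0.625. An AR(1) factor of 0.516 comes about as close and uses every stated input. Only some credit, roughly 0.52–0.63, can be inferred.
- A reader might conclude either that 520 is a ceiling or that recruitment must grow. The article reports about 340 parental transplants in the United Kingdom in 2010–2015 alone, within a 1990–2020 window. Whether to enlarge or accept lower power is the sponsor's choice.

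**Conclusion.** The point holds. The stated 80% power is not supported by the calculation given, because it takes a repeated-measures credit for an outcome that each recipient contributes once, and the section names a procedure that does not match its own target. For a 0.10 difference, power is about 60–64% at 479 pairs and 63–68% at 520, falling to about 55–60% and 58–63% with 10% missingness. A true 10-point difference would be missed roughly 32–42% of the time at 520 pairs, against the 20% implied.

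These figures assume the arm rates shown, equal groups, follow-up to 60 months and, for the log-rank version, proportional hazards. They leave out the continuity correction that the plan says it applied; including it lowers two-proportion power by a further 3–4 percentage points. This is a mismatch between the sizing method and the endpoint. It does not put the value of the cohort itself in doubt.

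**What to change.** In Sample size calculation:

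- Replace the GEE time-averaged-difference calculation with one for a single first event per recipient: two proportions at 60 months, or log-rank/Cox, for maternal versus paternal kidneys.
- State the assumed rate in each arm and the expected number of events for each scenario.
- Restate the conclusion: 520 pairs give about 58–68% power for a 10-point difference, depending on arm rates and missingness, and 80% power for about 12–13 points (HR roughly 1.4–1.6).
- Remove the wording on repeated measures, their correlation and continuous means, and redraw Fig. 2 against event rate and missingness.

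If the investigators do intend a repeated-measures analysis, the article must instead say what is measured four times and describe that analysis.

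The cost is one rewritten section, one figure and a less favourable power statement.

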**Fig. 2 Fig2:**
[figure not shown]
Projected sample size calculation using a generalized estimating equation approach with at least four repeated measures of the primary outcome, according to varying base correlation of 0.2 to 0.7 (between repeated measures) and degree of missingness of 0.0 to 0.15. A sample size of 479 donor/recipient pairs (1:1 allocation to maternal and paternal door kidneys, represented by discontinuous blue line) will be required to achieve a power of 80% with a two-sided significance of 5% for detecting a difference of 0.10 between marginal proportions after applying continuity correction (and correlations score of 0.5 of at least 4 observations [for the composite outcome measures], and accounting for potential missingness of data of up to 10%)

Between 2015 and 2018, there were 182 pediatric and adolescent patients aged ≤18 years with kidney failure in Australia who received a kidney transplants, with parental donor kidney transplants contributing 40% of total transplants. This compared with 30 patients in New Zealand (67% parental donor kidney transplants) and 30 patients in the Netherlands (30-40% parental donor kidney transplants) in the same time-period. In the United Kingdom, there were 760 pediatric and adolescent patients who received kidney transplants between 2010 and 2015, with approximately 340 (45%) parental donor kidney transplants. These recent figures suggest that the target sample size (to recruit 520 donor/recipient pairs between 1990 and 2020) is achievable.

### Statistical analysis

Data will be presented as mean ± standard deviation (SD) or number (proportion) for continuous and categorical variables, respectively, with means and proportion compared using *t-test* and the chi-squared test where appropriate. We will develop models with different numbers of archetypes and choose which to use as the final model according to the residual sum of squares using the “elbow” method [47]. The archetypal models will assign scores based on a combination of pre-transplant immunological and clinical (donor, recipient and transplant) parameters to each recipient using the time from transplant to the composite primary outcomes of de novo DSA, any episodes of acute rejection and allograft loss; with the scores totalling 1. Each parameter will be assigned to a single archetype cluster on the basis of the highest archetype score (corresponding to “high immunogenic risk” profile, comprising of immunological risk factors). Additional models accounting for pre- and post-transplant factors (such as donor age, non-adherence) will also be constructed. A principal component analysis will be constructed to visualize the data matrix used as the input for the archetypal analysis. The principal component analyses will produce two main results: (i) a correlation circle, and (ii) a projection of the individuals. The correlation circle allows for a graphical examination of the relationships among the pre-transplant immunological and clinical parameters and the graphical parameter contribution of the axes (positive or negative contribution: vector direction; strength of the contribution: vector length when projected on the axis). We will identify distinct groups (i.e. archetypes), each comprising of a well-defined set of immunological and clinical parameters that may improve the risk stratification for “adverse immunological outcomes” for those accepting a parental donor kidney for transplantation, and separately for those who have received maternal or paternal donor kidneys. The Australian and New Zealand cohorts will be the derivation cohort for these archetypes, which will be validated in the cohorts from the United Kingdom and the Netherlands. We will next seek to build a predictive model (combined cohorts) to examine the associations between the archetype clusters and other pre-specified covariates and the primary outcome using univariate Cox proportional hazards regression models. A multivariable Cox model will be constructed by selecting covariates by Group Lasso and Doubly Robust Estimation (GLiDeR), a method of variable selection to identify confounders using an adaptive group lasso approach that simultaneously performs coefficient selection, regularisation, and estimation across the treatment and outcome models. Bootstrap resampling with replacement or subsampling without replacement will be used to investigate and quantify model stability. Separate models will be constructed for each of the secondary outcomes. The results of the model and covariates will be reviewed to ensure clinical relevance. Deviance and score residuals will be plotted to evaluate for poorly predicted individuals or individuals that may have had large influences on model parameters. The performance of the integrated prognostic model will be assessed by computing a non–time-specific area under the curve (AUC) using the measure of concordance from Somer’s Dxy statistic. For assessment of model calibration, patients will be risk-stratified on the basis of their predictive index, which is the linear combination of the product of the multivariate model β coefficients and their individual covariate values. Kaplan-Meier survival curves will then be plotted for patients who are stratified into quintiles of their predictive indices. The validation cohort’s AUC will be determined and predicted and observed mortalities will be compared. The association between archetypes and adverse outcomes will be examined in the prospective cohort, and to examine how the addition of other newly developed novel immunological assays will improve the test performance of the models.

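### As written, archetype scores use time to the primary outcome and are then tested against that outcome in the combined cohorts; the scoring step must be restated without it

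*Protocol article*

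**What the plan says.** All of this stands in the protocol article, Methods/design, Statistical analysis.

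- Scoring: "The archetypal models will assign scores based on a combination of pre-transplant immunological and clinical (donor, recipient and transplant) parameters", and the same sentence continues "to each recipient using the time from transplant to the composite primary outcomes of de novo DSA", acute rejection and allograft loss. The scores total 1 for each recipient.
- Assignment: "Each parameter will be assigned to a single archetype cluster on the basis of the highest archetype score".
- Extra models: "Additional models accounting for pre- and post-transplant factors (such as donor age, non-adherence) will also be constructed".
- Derivation and validation: archetypes come from the Australian and New Zealand cohorts, "which will be validated in the cohorts from the United Kingdom and the Netherlands".
- Outcome model: "We will next seek to build a predictive model (combined cohorts) to examine the associations between the archetype clusters". These are Cox models, and their endpoint is the primary outcome itself.

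The number of archetypes is chosen by an elbow rule on the residual sum of squares. The PCA is said to display the archetypal input matrix, and its correlation circle is described for pre-transplant parameters only. A validation AUC and a later look in a prospective cohort are also planned. The article does not say whether UK and Netherlands recipients are scored with or without their own outcome time.

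**The concern.** If follow-up time to the composite outcome helps to place recipients in clusters, the clusters carry outcome information before any outcome model is fitted. A Cox model of the same outcome on those clusters then partly predicts the outcome from itself.

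Aim (ii) in the Background is exactly this association between immunological risk profile and adverse outcome, so an inflated test bears on a main conclusion. The intended use, helping families choose between parental donors, also requires a score that can be computed before transplantation, when no outcome time exists.

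A secondary question concerns the additional models. Archetypal analysis uses one row per recipient, so a factor that accrues during follow-up, such as non-adherence, could enter as a fixed value that depends on how long the recipient was observed.

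**Working it through.** The plan states no figure on this point, so there is none to reproduce. The check is a simulation in which no input is related to outcome.

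**Inputs from the article (Sample size calculation):** 520 pairs; 40% with the composite outcome by 60 months; two-sided 5% test.

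**Assumptions not in the article:** 5, 10 or 20 baseline inputs, mutually correlated; 3 or 4 archetypes; 170 derivation and 350 validation recipients; outcome time entered as one standardised column of follow-up time censored at 60 months; 200 runs per setting.

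**Steps.**
1. Event times are exponential with rate −ln(1 − 0.40)/60 = 0.5108/60 = 0.0085 per month, independent of all inputs.
2. Archetypal analysis gives scores summing to 1, and each recipient goes to the highest-scoring archetype.
3. A Cox score (log-rank) test compares clusters at 0.05.

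**False-positive rates (%):**

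| Inputs / archetypes | A: no outcome in scores | B: outcome in scores, all 520 | C: outcome in 170 only, tested in 520 | D: 350 re-scored with own outcome | E: 350 scored from baseline only |
|---|---|---|---|---|---|
| 5 / 3 | 4.5 | 96 | 54.5 | 85 | 2.5 |
| 5 / 4 | 6.5 | 99.5 | 82 | 97.5 | 3 |
| 10 / 3 | 5.5 | 68 | 21.5 | 46 | 5 |
| 10 / 4 | 5.5 | 88.5 | 48.5 | 85 | 5 |
| 20 / 3 | 4.5 | 32 | 8.5 | 13 | 6 |
| 20 / 4 | 7.5 | 70 | 25.5 | 56 | 6.5 |

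In C, archetypes are derived with the outcome in the 170, the other 350 are scored without it, and all 520 are tested together. In D and E the archetypes are also derived with the outcome in the 170, but only the 350 are tested.

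The Monte Carlo standard error at 5% is √(0.05 × 0.95/200) = 0.015, so 2% to 8% is compatible with nominal. Columns A and E lie inside that range. Columns B and D lie outside it throughout. Column C also exceeds it, but only just at 20 inputs and 3 archetypes.

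A separate implementation with 35% events (an assumption) and 100 datasets per setting gave 87%, 99%, 69% and 82% for 10/3, 10/4, 20/3 and 20/4, against 4% to 10% without outcome time. The direction agrees, but the size depends on the settings.

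**Post-transplant factor, conditional check.** Non-adherence with no true effect, ever present by 60 months in 10% or 30% (assumed), was entered as a fixed covariate in a Cox model, with 1,000 runs. If it is recorded only until the event, false positives are 64.5% and 99.3%, with median hazard ratios of 0.48 and 0.45. If it is recorded over a fixed window independent of the event, false positives are 5.5% and 4.7%.

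**The case against.** The strongest reply is that the scoring phrase is only awkward English for naming the endpoint. The same sentence bases the scores on pre-transplant parameters, the PCA text describes an input matrix of such parameters, and the elbow rule makes no use of the outcome. On that reading the circularity disappears. This reading is plausible, but it does not cancel the literal instruction: an analyst following the sentence would put outcome time into the scoring.

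The second reply is the external validation. It stands in part. Column E shows an honest test even when the outcome was used in derivation. Column D shows that the protection is lost if validation recipients are scored with their own outcome, and the article does not exclude this. Nor does the validation protect the combined-cohort Cox model (columns B and C). The prospective cohort could help too, but the article does not describe it elsewhere; the design section covers transplants from 1990 to 2020.

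Three stronger readings are tempting and are not supported:

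- That an association is guaranteed. The simulated rate is as low as 32% and falls as more baseline inputs dilute the outcome column. The article lists many candidate inputs, and neither simulation models that set.
- That the main archetypes contain post-transplant data. Such factors appear only in additional models, and one of the two named examples, donor age, is a baseline factor. The simulated hazard ratios for non-adherence describe one assumed recording mechanism, not this plan. The section on clinical and laboratory parameters gives no time window for non-adherence, and coding detail may properly sit in an analysis plan.
- That assigning parameters rather than recipients to clusters is an analytic error. The neighbouring text gives scores to recipients, so this is a slip of wording.

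**Conclusion.** The point holds in conditional form. Read literally, the outcome helps to form the predictor and is then predicted by it, in data that include the derivation cohort. Under the assumptions above, the nominal 5% error rate becomes 32% to 99.5% if everyone is scored with outcome time, and 8.5% to 82% if only the derivation recipients are. With pre-transplant inputs alone it stays at 4.5% to 7.5%. The simulation measured false positives only; the upward bias in hazard ratios and AUC follows from the same mechanism but was not quantified.

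If the outcome-free reading is what was meant, the planned analysis is sound on this point and only the text is wrong. The article does not settle which is meant, and the answer changes what aim (ii) can conclude, so the text must be corrected before analysis. The post-transplant issue is secondary: a bias arises only if factors recorded up to or after the event are treated as fixed.

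**What to change.** Amend the Statistical analysis text, and the analysis plan to match:

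1. Remove outcome time from the scoring step. State that archetypes and scores use pre-transplant immunological and clinical parameters only.
2. State that each recipient, not each parameter, is assigned by highest score.
3. Freeze the archetypes in the Australia/New Zealand cohort before any outcome model is fitted, and score UK and Netherlands recipients from their baseline inputs alone.
4. Report the association and AUC in the UK/Netherlands alone. If the combined cohorts are used, apply an optimism correction that repeats the archetype step inside every bootstrap sample.
5. In the additional models, enter factors that accrue during follow-up as time-dependent covariates or from a landmark.

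The cost is wording and some programming, with no new data. Apparent associations will be weaker, and an estimate from the UK/Netherlands alone rests on fewer recipients than the combined cohorts.
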